#### Recruitment

The pathway for parents participating in the RCT is similar to the current parent support pathway at Open Door, with parents being referred from other NHS services or self-referring. Upon referral, parents will be placed onto a waitlist, and prior to inclusion in the trial they will be contacted by a Research Assistant (RA) to ascertain suitability to participate. Participants will receive a phone call to inform them of the study and offer the opportunity to participate. Once consent to participate is obtained parents will complete the baseline battery and be given a participant number to identify participants anonymously. Participants randomised into APT will start treatment immediately, providing a further incentive to agree to randomisations. Those randomised to waitlist will receive the APT treatment after no more than 25 weeks. Once randomised, parents will be asked for consent to contact their adolescent and if granted, contact details will be obtained. The adolescent will be contacted by a RA, who will briefly explain the research. If the adolescent agrees to participate they will be sent a link via email and text message containing a participant information sheet, a consent/assent form, and the baseline adolescent battery. Recruitment is expected to be completed in Summer 2026.

## Methods: assignment of interventions

### Randomisation

#### Sequence generation

Eligible participants who provide written informed consent will be randomly assigned to one of two groups: the APT intervention group or the waitlist control group. The randomisation unit is the family of the consulting parent. The randomisation process will employ a 1:1 allocation ratio. Restricted stratified block randomisation is used with three blocking variables: consulting parent’s age, gender and education. These variables were significantly related to the intervention’s outcome in the previous pilot study.

#### Allocation concealment mechanism

Following baseline data collection, the RA will contact the collaborating statistician to randomly allocate the participant to APT or WL. RAs will be blind to group allocation.

#### Implementation

The collaborating statistician will have access to the random allocation sequence and randomly allocate participants to APT or WL. The RA will enroll participants into the study. The RA will not have access to the random allocation sequence. The random allocation list will be stored on a secure electronic database, compliant with data protection regulations to ensure confidentiality and integrity.

#### Blinding

An independent statistician will manage the randomisation process to ensure impartiality. Due to the nature of the waitlist control design, participants and therapists will not be blinded to allocation. However, to maintain the integrity of the study, RAs responsible for collecting outcome data will remain blind to group allocations. This blinding reduces the risk of bias during data collection and ensures the reliability of the results.

#### Data collection methods

All data is collected by the RA. RAs involved in data collection will receive standardised training on study protocols, ethical considerations and administration of measures. For both parents and adolescents in the APT treatment group, data are self-reports completed by the parent or adolescent and collected at four time points: T1 (pre-intervention) baseline, T2 (after six sessions, end-of-treatment), and follow-ups at both T3 (three) and T4 (six months) following the end of treatment. For WL participants data are self-reports completed by the parent or adolescent and collected at six time points. T1 (Following randomisation), T2 (six weeks later), T3 (three months – end of WL beginning of treatment), T4 (end- of-treatment) and follow-ups at both T5 (three) and T6 (six months) following the end of treatment. Participating parents will be offered the choice of completing the battery in a paper or online format.

Data collection instruments for parent measures include the primary outcome measure: SIPA [17], which has excellent internal consistency and content validity [18].

Regarding the secondary outcome parent measures: The SDQ is effective in detecting mental health problems [19]. The PHQ-9 demonstrates strong psychometric properties [20, 21], as does the GAD-7 [22, 23]. The APQ-SF shows good criterion validity in differentiating clinical and nonclinical groups [24–26]. The CBQ has good discriminant validity in distinguishing between distressed and non-distressed families [27]. The Parenting Scale has good psychometric properties for measuring parental discipline styles, with internal consistency and validity, including in clinical populations [28, 29]. The RFQ has demonstrated adequate reliability and validity [30]. The WAI-SF-C shows excellent psychometric properties, with Cronbach’s alphas ranging from 0.85 to 0.90 for subscales and 0.91 to 0.92 for total scores [31, 32]. The Goal Based Measure is sensitive to change and valid for tracking progress towards goals [33].

For the adolescent battery, the SDQ-YP, APQ-YP, and RFQ demonstrate comparable psychometric properties to their parent-report counterparts [19, 24–26, 30]. Adolescent batteries will be completed online, and adolescents will be compensated with a £10 e-voucher for each completed test battery.

Therapists will complete a battery at the end of treatment. The psychotherapist battery includes the WAI-SF-T [31, 32]. APT supervisors will complete an observer battery on a randomly selected session’s video for participants who have consented to video recorded sessions. The observer battery includes Adherence to the APT model. Data collection forms can be accessed at UCL data repository.

To promote completion of follow ups and prevent missing data, participants will be informed of the timeline of the research study, that questionnaires will be completed at the start of the study, 6 weeks later, at 3 months follow up, and at 6 month follow up. Participants will be informed that if they are allocated to the waiting group, questionnaires will also be completed at the end of treatment, and at 3 and 6-month follow ups. To promote completion, the RA will phone parents the week before follow-up questionnaires are due, reminding participants that this is an essential part of the research to be completed at certain time points, and ask participants to re-score goals, which are sent via email. The RA will contact the parent weekly until questionnaires and goals are returned. Adolescent participants are sent questionnaires the week before measures are due, the RA will contact the YP up to 3 times (weekly) if these are unreturned.

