### Intervention and comparator

The aim of APT is to help the parent in the parenting of their adolescent and improve the adolescent-parent relationship. APT facilitates a collaborative relationship between the therapist and parent to develop parenting strategies, provide psychoeducation, and practice and reflect on behavioural experiments. Through this, APT aims to create a more balanced relationship between the parent and adolescent, where the adolescents’ views and feelings are considered, communication, boundaries and the relationship between parent and adolescent is explored, and the parent develops an enhanced understanding of their parental identity and role.

The APT intervention can be delivered one-to-one or with a couple. Participants will receive six weekly 50-min appointments, with the option of a 7th review session. Adolescents will be invited to attend one session; this is optional, and adolescents are not required to attend. The sessions will be delivered in person at one of the two clinical sites, or via video appointment. This allows for meeting parents’ delivery preferences to increase accessibility to the intervention.

Participants will be randomised into the APT intervention group or waiting list control group. Those randomised to waitlist will receive the APT treatment after no more than 25 weeks. Following randomisation, participants in the APT group will begin treatment. After six sessions of APT, the end-of-treatment battery will be administered to all participants (those in both APT and WL groups). The same battery will be administered to all participants again three months and six months following the end of treatment. After three months of randomisation, participants in the WL condition will be offered APT. These parents will be administered all test batteries from pre-treatment to six-month follow-up. Participants can withdraw from the study at any time. No concomitant care is permitted during the trial.

Fidelity of APT delivery to the APT model will be assessed through checklists completed by observers (see Outcomes section).
[figure not shown]

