### Statistical methods

The primary analysis will compare the effectiveness of APT to the waitlist control condition, focusing on the SIPA scores at post-intervention. The primary outcome variable will be analysed using between-groups mean differences, and effect sizes will be calculated for the end-of-treatment and three- and six-month follow-ups. Outcomes will be predicted by mixed-effects linear regressions with special interest in allocation group and baseline group differences (if any). Secondary outcome variables will be analysed using mixed-effects models (linear and nonlinear, logistic or Poisson as appropriate). Partner attendance, adolescent attendance, working alliance and reflective function will be assessed in their role as predictors and/or mediators of change. The unit of analysis will be the referred parent, even when they have attended APT with their partner. Maintenance of effects will be examined by comparing outcomes at the six-month follow-up to post-intervention scores. An intention-to-treat approach will be employed for all analyses, ensuring that participants are analysed in the groups to which they were originally assigned, regardless of adherence to the intervention protocol.

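### The primary time point T2 has inconsistent definitions: six completed sessions in the APT arm, six calendar weeks on the waitlist, with no rule for late or unfinished treatment

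*Protocol article*

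**What the plan says.** The Statistical methods section of the protocol article places the primary comparison at post-intervention, so T2 carries the main result. Three statements fix when T2 happens.

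- *Data collection methods, schedule by arm.* For APT: "T2 (after six sessions, end-of-treatment), and follow-ups at both T3 (three) and T4 (six months) following the end of treatment". For the waitlist: "T1 (Following randomisation), T2 (six weeks later), T3 (three months – end of WL beginning of treatment"). One is an event, the other a date.
- *Intervention and comparator.* "After six sessions of APT, the end-of-treatment battery will be administered to all participants (those in both APT and WL groups"). Here both arms wait for six sessions, which waitlist parents have not had at that stage.
- *Data collection methods, reminders.* Parents are told that "questionnaires will be completed at the start of the study, 6 weeks later, at 3 months follow up, and at 6 month follow up". This is a calendar rule without distinction by arm.

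Two other statements matter. The Statistical methods section promises intention-to-treat analysis "regardless of adherence to the intervention protocol". The Blinding section states that "RAs responsible for collecting outcome data will remain blind to group allocations".

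**The concern.** In a two-arm comparison at a single time point, both arms should be measured at the same distance from randomisation, and the due date should not depend on what happens after randomisation. A T2 that waits for the sixth session fails on both counts. A postponed session or a late first appointment moves the APT assessment while the waitlist assessment stays where it is, so part of the difference between arms could reflect elapsed time. A parent who leaves treatment early has no T2 event under that rule, so whether the primary outcome is collected could depend on treatment completion in one arm only. Intention to treat is meant to exclude that dependence.

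There is a practical side too. Research assistants collect all data and telephone parents the week before follow-up questionnaires are due. If the APT due date depends on session count, whoever schedules it needs session status, and that reveals the arm.

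**Working it through.** The plan gives no figure for the interval between arms at T2, so there is none to reproduce. The check sets the rules side by side and then counts weeks.

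**1. The rules side by side**

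| Place in protocol | APT arm | Waitlist arm |
|---|---|---|
| Data collection methods, schedule | after six sessions | six weeks after T1 |
| Intervention and comparator | after six sessions of APT | after six sessions of APT |
| Data collection methods, reminders | six weeks after start | six weeks after start |

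The first row differs between arms, the second gives the waitlist a trigger it cannot yet meet, and the third contradicts the first for APT. Nothing says which governs. The end of treatment is itself slightly open: "Participants will receive six weekly 50-min appointments, with the option of a 7th review session".

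**2. Where the triggers fall if all goes to plan**

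Inputs: weekly sessions (Intervention and comparator), immediate start for APT (Recruitment), waitlist T2 at week 6 (Data collection methods).

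Week of session six = start delay + 5 + missed weeks, because six weekly sessions span five intervals.

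- Start at once, none missed: 0 + 5 + 0 = week 5, a gap of 5 − 6 = −1 week.
- Start one week on, none missed: 1 + 5 + 0 = week 6, a gap of 0.

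So the two rules nominally agree to within a week.

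**3. Where they fall if sessions slip**

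The documents give no delivery data. Start delays of 0 to 2 weeks and 0 to 3 missed weeks are assumptions. Each cell shows the week of session six, with the gap against week 6 in brackets.

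| Start delay (weeks) | 0 missed | 1 missed | 2 missed | 3 missed |
|---|---|---|---|---|
| 0 | 5 (−1) | 6 (0) | 7 (+1) | 8 (+2) |
| 1 | 6 (0) | 7 (+1) | 8 (+2) | 9 (+3) |
| 2 | 7 (+1) | 8 (+2) | 9 (+3) | 10 (+4) |

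The range is −1 to +4 weeks. A date counted from randomisation makes the scheduled gap zero in every cell.

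**4. Parents who stop early**

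Under the arm-specific schedule and under the intervention section, an APT parent with fewer than six sessions does not meet the stated condition. Under the reminder text the same parent is due at six weeks. The intention-to-treat statement needs the second reading. The collection schedule states the first.

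**5. Room for a common date**

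Waitlist parents are offered APT from three months, about week 13. The latest session six in the table is week 10, so even under these assumptions a common T2 can sit before waitlist treatment begins.

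**The case against.** The strongest reply is that the passages, read together, describe one visit at about week 6. Sessions are weekly, APT starts at once, a single battery goes to both arms, and everyone is told six weeks. The reminder text also gives every parent a due date and has the research assistant chase weekly until questionnaires come back, with no condition on attendance. The schedule figure is not visible in the text reviewed and may show a common T2 column.

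Much of this stands. The text does not fix different assessment times for the arms, and it is too strong to say that parents who stop early have no T2 date anywhere. What remains is that the passage setting out data collection by arm says something else for APT, and nothing visible says which rule wins.

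A reader might go further in four ways that the documents do not support.

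- *A bias of known size.* Multiplying 2 to 4 extra weeks by an untreated improvement of 0.02 to 0.05 SD per week gives 0.04 to 0.20 SD. Both inputs are assumed, and the product leaves out the zero and negative gaps in the table.
- *Missing outcomes in 13 APT parents and no waitlist parents.* 0.325 × 40 = 13 is correct arithmetic, but the Sample size section applies 32.5% attrition to the whole sample. It does not equate attrition with unfinished treatment, and waitlist parents can be lost too.
- *Bias certain to favour APT and beyond repair by analysis.* Why parents stop is unknown, and some may leave because they have improved. The planned mixed-effects models can use partial data, so neither part of the claim is shown.
- *Research assistant blinding bound to fail.* No passage says that they count sessions, and on the six-week date they would not need to. The SIPA is self-reported, which limits what an unblinded assistant could change.

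**Conclusion.** The point holds as an inconsistency in the definition of the primary time point. Two passages tie APT's T2 to six sessions, one of them ties the waitlist to those sessions as well, and the remaining statements use six weeks. On the nominal timetable the difference is at most about a week. It grows only if sessions start late or are missed, to an illustrative +4 weeks under the assumptions shown. The session-based rule also conflicts with the intention-to-treat statement, because parents who stop early do not reach the event.

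Whether this would bias the result, by how much and in which direction cannot be settled from the documents. The case for change rests on the conflict between passages and on the low cost of removing it. The blinding argument is supporting only.

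**What to change.** Reconcile the three statements in Intervention and comparator and Data collection methods to one rule:

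- Set T2 at the same number of weeks from randomisation, with the same window, in both arms, and before waitlist parents start APT at three months.
- Collect T2 from every randomised parent, whatever the number of sessions attended.
- Record the number of sessions attended by T2.

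The documents contain no session dates, so the team must choose the week from its own knowledge of delivery. An earlier week catches more parents before their last session; a later one comes closer to the start of waitlist treatment. A fixed date also lets research assistants schedule T2 without session status, which supports the blinding the protocol states.

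The cost is revised schedule wording and reminders, plus an amendment, which under Protocol amendments needs ethics committee and sponsor approval if substantial. Some APT parents may be assessed before their last session, which slightly dilutes the estimate. Any parents already assessed under the present wording would have followed a different rule, so the actual T2 date should be kept for everyone. The later visits do not need to be re-anchored to settle this point.

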#### Data management

All data will be collected through online forms completed by participants to reduce errors associated with data entry. Open Door is committed to safeguarding the privacy of their users and the same privacy rules will be applied to participants of this study. All data will be kept for a maximum of seven years after the study has ended and will be stored in a GDPR secure data management service. All data will be collected and stored in accordance with the Data Protection Act 2018. If a participant withdraws from the study, they can request to have their data and contact details deleted or allow us to keep the data. In the case of keeping the data, the research team will use the minimum personally-identifiable data possible to safeguard participants' rights (i.e. delete contact details and keep anonymous questionnaire data). Video recordings are for the purposes of maintaining quality of treatment and providing supervision to therapists. Participants will be informed of how video recording will be used and consent for video recording will be sought before taking part in the study. Recordings will be kept on a securely stored, encrypted file and will only be used by participants' therapist and their supervisor during supervision and will not be shared with anyone else. After completion of therapy, all videos will be deleted. Participants can withdraw consent for video recording at any time, at which point all videos will be deleted.

### Statistical methods

The primary analysis will compare the effectiveness of APT to the waitlist control condition, focusing on the SIPA scores at post-intervention. The primary outcome variable will be analysed using between-groups mean differences, and effect sizes will be calculated for the end-of-treatment and three- and six-month follow-ups. Outcomes will be predicted by mixed-effects linear regressions with special interest in allocation group and baseline group differences (if any). Secondary outcome variables will be analysed using mixed-effects models (linear and nonlinear, logistic or Poisson as appropriate). Partner attendance, adolescent attendance, working alliance and reflective function will be assessed in their role as predictors and/or mediators of change. The unit of analysis will be the referred parent, even when they have attended APT with their partner. Maintenance of effects will be examined by comparing outcomes at the six-month follow-up to post-intervention scores. An intention-to-treat approach will be employed for all analyses, ensuring that participants are analysed in the groups to which they were originally assigned, regardless of adherence to the intervention protocol.

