**Methods:**

Participants will be parents of adolescents who self-refer to Open Door, reporting clinically significant levels of parenting stress through the SIPA. Participants will be randomly allocated to receive the APT intervention or waitlist control. The primary outcome measure will be the SIPA, measuring parenting stress, the parent-adolescent relationship, adolescent and parent wellbeing, and mental health outcomes. Secondary outcome measures measure mediators of change and adherence to APT. Results on outcome measures will be compared between the APT group and control group immediately following the intervention, three months post intervention, and six months post intervention.

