This paper outlines the protocol for a randomised controlled trial (RCT) to measure the effectiveness of Open Door’s APT intervention. APT is a brief, manualised parenting intervention for clinically stressed parents of adolescents, with a particular focus on the adolescent-parent relationship. APT can be delivered face-to-face or digitally over six sessions. APT follows the Open Door APT manual, which is a six-session model. The APT manual contains guidance on applying APT to practice, core techniques, and step-by-step guides for sessions one to six as well as working with the adolescent and parent, working with couples, and additional considerations. Clinicians use the manual and follow a checklist for each session, which contains actions for each session.

Findings from its preliminary evaluation, a pre-post pilot study of 279 parents, demonstrated promising results, particularly in terms of feasibility, acceptability, and real-world effectiveness [14]. However, a significant limitation of this study was the lack of a control group and follow-up measures to demonstrate long-term effectiveness. Furthermore, as highlighted in intervention development frameworks [15, 16], an RCT is essential to establish the efficacy of an intervention and elucidate the mechanisms by which it achieves its effects. This trial will randomly assign parents to either an active group (complete the APT intervention immediately) or control group (placed on a waitlist). A waitlist control comparator group was chosen to ethically allow all participants access to the APT intervention while providing a baseline comparison against immediate treatment. Results on outcome measures will be compared between groups after the intervention, and at three and six month follow up intervals. This trial therefore builds on the pre-post study through ruling out spontaneous recovery and capturing long-term improvements. This trial will provide robust evidence regarding the effectiveness of a brief, individualised parenting intervention tailored for parents of adolescents. If effective, APT has the potential to offer a scalable solution to support parents and improve outcomes for adolescents and their families. By presenting this RCT protocol, this paper lays the groundwork for the next crucial step in establishing APT as a robust, evidence-based intervention.

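### The three- and six-month follow-up contrasts are planned as APT versus waitlist, but waitlist parents are offered APT from three months, so no untreated control arm remains at six months and possibly none at three

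*Protocol article*

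**What the plan says.** **The planned contrast.** Statistical methods focuses the primary analysis on SIPA at post-intervention, by intention to treat, and adds that "effect sizes will be calculated for the end-of-treatment and three- and six-month follow-ups", in the same sentence that specifies between-group mean differences. The Methods paragraph of the Abstract says that outcomes will be "compared between the APT group and control group immediately following the intervention, three months post intervention, and six months post intervention". Background and rationale repeats the between-group comparison at both follow-ups.

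**When the waitlist arm is treated.** Intervention and comparator says: "After three months of randomisation, participants in the WL condition will be offered APT". Data collection methods agrees, describing the waitlist arm's three-month assessment (its T3) as "end of WL beginning of treatment". Intervention and comparator, and again Recruitment, also say: "Those randomised to waitlist will receive the APT treatment after no more than 25 weeks".

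**When follow-up is measured.** Data collection methods times the APT arm's T3 and T4 at three and six months from the end of treatment, not from randomisation.

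**What is claimed.** Background and rationale says: "This trial therefore builds on the pre-post study through ruling out spontaneous recovery and capturing long-term improvements". Objectives makes maintenance at three and six months an aim. The Discussion names non-specific treatment effects as the limitation of a waitlist control. It does not mention that the control arm is treated during follow-up.

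**The concern.** A waitlist comparator estimates the effect of APT against no APT only while the waitlist arm is waiting. Once those parents start APT, a comparison of the arms as randomised answers a different question: starting APT now against starting it some months later. The protocol describes the follow-up results as APT against control throughout.

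A small or null difference at six months could be read as loss of effect, when it may only mean that both arms have been treated. If effects fade with time since treatment, the difference could even favour the waitlist arm, whose treatment is more recent. Long-term benefit is one of the two advances the protocol claims over the uncontrolled pilot, so the label affects a main conclusion of the trial.

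**Working it through.** **Inputs**
- APT lasts six weekly sessions, taken as 6 weeks (Intervention and comparator). The APT arm starts immediately after randomisation (Recruitment), taken as week 0.
- APT-arm follow-ups are 3 and 6 months after end of treatment (Data collection methods).
- Waitlist APT starts at 3 months (Intervention and comparator; Data collection methods), or by week 25 at the latest (Intervention and comparator; Recruitment).
- Conversion: 3 months = 3 × 365.25 / 12 / 7 = 13.04 weeks; 6 months = 26.09 weeks.

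**APT-arm assessments, in weeks from randomisation**
- End of treatment: 6
- Three-month follow-up: 6 + 13.04 = 19.0
- Six-month follow-up: 6 + 26.09 = 32.1

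**Waitlist treatment window**
- Three-month rule: start 13.0, end 13.04 + 6 = 19.0
- 25-week maximum: start 25, end 25 + 6 = 31

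**Waitlist status at each APT-arm assessment, for parents who take up the offer**

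| APT-arm assessment | Three-month rule | 25-week maximum |
|---|---|---|
| Week 6.0 | untreated | untreated |
| Week 19.0 | just finished APT | untreated |
| Week 32.1 | 13.0 weeks after APT | 1.1 weeks after APT |

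Only the week-6 contrast is APT against untreated waitlist under every stated timing. At week 19 the answer depends on which waiting statement operates. At week 32 neither leaves an untreated arm.

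**Size.** The protocol gives no expected follow-up contrast to reproduce. As an illustration, take its design effect of d = 0.4 and assume that it is the same in both arms, lasts, and is zero in parents not yet treated. With share p of the waitlist arm treated by the assessment, the expected intention-to-treat contrast is 0.4 × (1 − p):
- p = 0.50: 0.4 × 0.50 = 0.20
- p = 0.80: 0.4 × 0.20 = 0.08
- p = 1.00: 0.4 × 0 = 0

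At p = 0, possible at three months if everyone is still waiting, the contrast keeps its full 0.4.

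**The case against.** **The primary analysis is sound.** This stands. It is set at post-intervention, about week 6, before any waitlist parent starts APT. The point concerns the follow-up contrasts and the claims built on them.

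**A reader might infer that both follow-up contrasts compare wholly treated arms, with an expected difference of zero.** The documents do not support that. Parents are offered APT and may decline it, so the share treated is unknown. At three months, waits towards 25 weeks would leave an untreated comparator. Under the maximum wait, finishing before the six-month visit also rests on a margin of about one week, with no missed sessions and no optional seventh session. A delay there would mean that treatment was still in progress, not that the arm was untreated.

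**The follow-ups might be counted from the start of the study.** The description in Data collection methods of what participants are told can be read this way. A three-month contrast at week 13 could then be clean if both arms were assessed before waitlist treatment began. Six months would be week 26.1: about 7 weeks after waitlist APT ended under the three-month rule, or about one week into it under the maximum wait. However, the schedule in the same section fixes the APT arm's follow-ups from end of treatment.

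**A reader might infer that the mixed model will align the arms by visit number, or that the waitlist visit counts conflict.** The protocol does not say how time is coded, and that is commonly left to the analysis plan. The list of questionnaires given to participants may name the same visit twice. Neither point is made here.

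**A reader might infer that the spontaneous-recovery claim fails.** The protocol gives it no time horizon. The week-6 contrast addresses it, and waitlist T3 observes the untreated course to three months. What lacks support is a controlled claim about the long term.

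**Later between-arm contrasts remain valid randomised comparisons.** This stands, provided that they are described as immediate versus delayed APT.

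**Conclusion.** The concern holds for the follow-up contrasts. As written, the protocol commits to APT-versus-waitlist effects at two follow-ups. At six months there is no untreated control arm under either stated waiting time. At three months there is one only as far as parents wait longer than three months. On the equal, lasting effect of d = 0.4 assumed above, the six-month contrast shrinks in proportion to uptake: half the effect remains at 50% uptake, a fifth at 80%, none at 100%. Actual uptake is not given. The timeline assumes an immediate start in the APT arm and six weekly sessions without gaps.

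The maintenance analysis compares six-month with post-intervention scores over time. That is a legitimate description, but it has no untreated comparator and should be labelled so.

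**What to change.** 1. Limit APT-versus-waitlist estimates to assessments made before waitlist crossover and matched on weeks since randomisation, with end of treatment as primary. A second such estimate at about three months from randomisation is possible only if both arms are assessed then, before waitlist treatment starts.
2. Report any later intention-to-treat contrast as immediate versus delayed APT, matched on weeks since randomisation. On the three-month schedule, the APT arm's T3 and T4 (weeks 19 and 32) coincide with the waitlist arm's T4 and T5.
3. Report maintenance as a within-arm estimate with a confidence interval, stated to be uncontrolled.
4. Do not adjust the randomised comparison for APT received after randomisation. Uptake is itself an outcome of the process, and adjusting for it would depart from the stated intention-to-treat approach.
5. Amend the Abstract, Background and rationale, Objectives and Statistical methods to match, so that no controlled long-term effect is claimed. Add the loss of the untreated arm to the limitations in the Discussion.
6. Ask the sponsor to reconcile the three-month offer with the 25-week maximum, since the comparator's status at three months depends on it.

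**Cost.** Items 2 to 6 and the core of item 1 are analysis and wording changes, with no extra participants. The optional three-month contrast in item 1 would need an APT-arm assessment at that week. The trial gives up a controlled long-term claim that its design cannot support.
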